### Study design

#### Study 1: the registry study

The consortium, drawing on extensive genetic epidemiology expertise, will leverage Swedish and Norwegian national registers and biobanks with (single-nucleotide polymorphism) SNP-array genotyped samples. It will begin by identifying adult Swedish residents from the Swedish National Patient Register and the Swedish Prescribed Drug Register, with registered treatment contact for BD. A similar process will be implemented with Norwegian registers. Subsequently, the consortium will investigate diagnosed MC, comparing individuals with and without BD. The primary focus of the Swedish and Norwegian teams is to explore the associations between BD onset and MC risk, with a specific emphasis on MetS. Additionally, it will include type 2 diabetes and CVD as relevant outcome variables due to their strong association with MetS. Research outcomes will be determined using a combination of diagnostic data from patient registers and pharmacological treatment details from the prescribed drug register, as shown in Table 2. Furthermore, risk prediction models for cardiometabolic conditions in individuals with BD will be developed, with CVD and type 2 diabetes as primary outcomes, and MetS, and all-cause and cause-specific mortality, as secondary outcomes. Given the absence of complete MetS diagnostic criteria in Swedish population registries, the consortium will use several related medical conditions as proxies (e.g., obesity, hypertension, hyper/dyslipidaemia). Access to genotyping data from approximately 1.3 million participants, derived from Illumina arrays or similar platforms in existing genotyped cohorts, will further enrich the study.

**Table 2 Tab2:** Socio-demographic and clinical characteristics to be used for the training set with the Swedish registry

1	Sex
2	Ethnicity
3	Age
4	Marital status
5	Children (yes/no)
6	Education years, Mean (SD)
7	Area of residence (urban/rural)
8	Current occupational status
9	Poverty (poor housing, malnutrition, etc.)
10	Age of first contact with mental health services (Years), Mean (SD)
11	Bipolar disorder I or II
12	Comorbidity with other mental disorders
13	Number of lifetime psychiatric hospitalizations
14	The overall length of psychiatric hospitalizations (months)
15	Lifetime substance or alcohol use disorder (yes/no)
16	Ever treated with lithium or mood stabilizers
17	Ever treated with antipsychotics
18	Number of diagnoses of MC lifetime

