19	Number of lifetime hospitalizations in any medical wards
20	Body Mass Index (BMI)
21	Information about all drug prescriptions in the lifetime
22	Smoking (yes/no)
23	Sleep problems
24	Familiarity with diabetes and/or CVD

While leveraging national registers offers significant advantages, several limitations will have to be considered when interpreting findings from this study. First, the reliance on proxy conditions to represent MetS may introduce potential misclassification bias. The absence of complete diagnostic data in the registries limits the study's ability to accurately capture the true prevalence of MetS among individuals with BD. Additionally, individual proxies might not fully capture the complex interplay of factors contributing to MetS, potentially underestimating the true association between MetS and these outcomes in BD. Second, the study is inherently limited to information available in the registers, which may lack granularity around certain lifestyle factors, clinical metrics, and disease progression markers over time. Lastly, the utilization of specific-cause mortality outcomes should also be interpreted with caution due to potential discrepancies between recorded and actual causes of death (Brooke et al. 2017).

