#### Study 1: the registry study

For prediction modelling studies in Sweden, we will employ multivariate Cox proportional hazards regression analysis to develop 1-, 2- and 5-year risk prediction models separately for: CVD, and type 2 diabetes, as primary outcomes, as well as for proxy measures of MetS—hypertension, obesity and hyper/dyslipidaemia, and all-cause and cause-specific mortality as secondary outcomes, in individuals with BD. This will be done by combining traditional risk factors of cardiometabolic disorders (i.e., age, sex, a diagnosis/medication prescription for hypertension, diabetes mellitus (type 1 and type 2), hyperlipidaemia, obesity, and smoking; and family history), with potentially relevant novel predictors associated with both BD and an increased risk of cardiometabolic conditions (i.e., psychiatric comorbidity, use of psychotropic medication, and socio-demographic factors). We will use a limited backward stepwise procedure to determine whether to retain novel candidate predictors based on their p-values. Traditional risk factors will be kept in the model. With this approach we aim to retain predictors considered as traditional cardiometabolic risk factors based on clinical practice and previous studies, and to consider potentially relevant novel risk factors, with the final model being easily applicable by clinician, with satisfactory face validity. A bootstrapping method will be used for internal validation of the models with 200 bootstrap samples. To assess the discrimination of the models, the ROC curve and C-index will be used. To assess the calibration of the models we will use the Integrated Brier Score and calibration plots. We will also compare the performance of the models that includes only traditional risk factors with the models that include additional novel risk factors by calculating the Net Reclassification Index (NRI) and the Integrated Discrimination Improvement (IDI) index. We will also test the performance of the models across the following subgroups: males/females, and aged younger than 50/50 and older. Machine Learning (ML) algorithms for survival analysis will be tested on Swedish and Norwegian register data, considering a large number of available potential risk indicators such as demographics, electronic medical records, and genotypes. The overarching research question is to explore if ML algorithms based on many predictors may improve the predictive accuracy. For the ML algorithms, the data will be split into a 60% training set, 20% validation set, and 20% test set. Four models will be trained: penalized Cox regression, random survival forest, gradient boosting machine, and survival support vector machine. Hyperparameters will be tuned on the validation set. Model discrimination will be evaluated with C-index and cumulative/dynamic AUC. Calibration will be assessed with the Integrated Brier Score. Performance metrics on the test set will determine the final model. Sensitivity analyses will explore model accuracy when considering predictors related to patient history and dispensed medications only. We will also assess model performance separately in Sweden and Norway. Furthermore, we will merge register data from Norway and Sweden with biobank data (N ~ 1.3 million) to evaluate whether adding genotypes improves predictive power.

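### The always-retained predictor list for the Study 1 Cox models contains four of the modelled outcomes, including the primary outcome type 2 diabetes, so the retention rule cannot be followed as written for those models

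*Protocol article*

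**What the plan says.** Under Data analyses, Study 1, the article plans "1-, 2- and 5-year risk prediction models separately for: CVD, and type 2 diabetes, as primary outcomes", and continues "as well as for proxy measures of MetS—hypertension, obesity and hyper/dyslipidaemia, and all-cause and cause-specific mortality as secondary outcomes".

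All these models draw on one list of traditional risk factors, introduced as a closed enumeration. Besides age and sex it contains "a diagnosis/medication prescription for hypertension, diabetes mellitus (type 1 and type 2), hyperlipidaemia, obesity, and smoking; and family history". Backward stepwise selection applies only to the other predictors; its purpose is "to determine whether to retain novel candidate predictors based on their p-values". For the listed factors the rule is "Traditional risk factors will be kept in the model".

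Under Study design, Study 1, the outcomes are defined from the same kind of register field: "Research outcomes will be determined using a combination of diagnostic data from patient registers and pharmacological treatment details".

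**The concern.** A condition is placed on both sides of the model, measured from diagnosis and dispensing records each time, and the predictor side is protected from removal. Two results are at stake for the affected models.

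- **Discrimination.** If the flag marks people who already have the outcome, the C-index measures how well existing disease is recorded, not how well new disease is foreseen.
- **The comparison of traditional with extended models.** NRI and IDI are to show what novel predictors add. A traditional-only model that already holds the outcome's own code leaves them little to add, so the comparison would say little about their value.

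Type 2 diabetes is one of two primary outcomes, so this is not confined to secondary work.

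**Working it through.** **1. The two lists side by side (Data analyses, Study 1).**

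| Modelled outcome | Role | On the retained list? |
|---|---|---|
| CVD | primary | no |
| Type 2 diabetes | primary | yes |
| Hypertension | secondary | yes |
| Obesity | secondary | yes |
| Hyper/dyslipidaemia | secondary | yes (as hyperlipidaemia) |
| All-cause and cause-specific mortality | secondary | no |

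Exactly four outcomes overlap.

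**2. What the rule does under each handling of existing cases.**

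- *Existing cases stay in and count as events.* The flag identifies events that have already happened, and the outcome predicts itself.
- *Existing cases are excluded.* The hypertension, obesity and hyperlipidaemia flags are zero for everyone left. A constant has no estimable coefficient, so the term cannot be kept. The same holds for a separate type 2 diabetes term. A combined diabetes term would survive only as type 1 diabetes and change its meaning.

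**3. Possible size in the first case (illustration).** Let q be the share with the condition at entry and r the share of the others who develop it. If every existing case counts as an event, the flag has specificity 1 and sensitivity q / (q + (1 − q)r). Its AUC alone is (1 + sensitivity)/2. The documents give neither q nor r for these conditions, so both are assumed. The top value of q borrows the article's 31% MetS prevalence.

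| q | AUC, r = 5% | AUC, r = 15% |
|---|---|---|
| 5% | 0.756 | 0.630 |
| 10% | 0.845 | 0.713 |
| 20% | 0.917 | 0.812 |
| 31% | 0.950 | 0.875 |

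For example, q = 31% and r = 5% give 0.31 / (0.31 + 0.69 × 0.05) = 0.31/0.3445 = 0.900, and (1 + 0.900)/2 = 0.950.

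**4. Sample size.** The article's inputs (Power and sample size, Study 1) are p = 24 candidate predictors, shrinkage S = 0.90 and R² = 0.05. The shrinkage criterion is n = p / [(S − 1) ln(1 − R²/S)].

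- p = 24: ln(1 − 0.05/0.90) = −0.05716, so n = 24/0.0057158 = 4,198.9, rounded up to 4,199. This reproduces the stated figure.
- p = 23, assuming the removed term is one of the 24: n = 4,023.9, rounded up to 4,024.

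Both are far below the planned cohort of 40,000.

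**5. Deaths before the event (side point).** With constant event rate λ and death rate μ per year, compare 1 − exp(−λt) with [λ/(λ + μ)][1 − exp(−(λ + μ)t)]. Assume λ = 1% and t = 5 years. At μ = 1% the values are 0.0488 and 0.0476, a ratio of 1.025. At μ = 4% they are 0.0488 and 0.0442, a ratio of 1.10. The relative excess is roughly μt/2, so about 0.5–2% at 1 year and 1–4% at 2 years. The rates are assumptions.

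**The case against.** The best defence is that the plan is about new disease. It uses time-to-event models, and the sample size section speaks of predicting MetS incidence. A patient with diabetes at entry has no first onset left to model, so existing cases would naturally be removed. Software would then drop the constant term, and C-index, NRI and IDI would be untouched. The retention sentence can also be read as only saying which predictors escape p-value selection. Finally, at-risk definitions, look-back windows and competing events are details that an article usually leaves to a fuller document.

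Much of this stands. A reader might infer that the reported performance for type 2 diabetes will be an artefact of leakage. The article does not support that, because it never says existing cases are kept and counted. The 12,000 expected events are derived from a prevalence, and the word incident there describes bipolar disorder, but a sample-size input is not a rule for counting events.

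A reader might also take Table 2, with items such as "Information about all drug prescriptions in the lifetime", as part of the forced set. It is not: the retained list is the traditional factors only. The 24 rows of Table 2 match the 24 candidate predictors in number, but the text does not name lifetime prescriptions or the comorbidity count among the Cox predictors.

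The lack of a stated method for competing deaths is mainly an omission. Cox models are compatible with correct absolute risks when event and death models are combined.

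What the defence does not remove is the overlap itself. The list is closed, the retention rule is unqualified, and the outcomes are named in the same paragraph. Even on the favourable reading, the stated rule cannot be carried out for these models.

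**Conclusion.** The point holds as a rule that is fixed badly. Four of the Study 1 Cox outcomes, one primary and three secondary, are also predictors that the text says are always kept. Read literally, the rule yields self-prediction if existing cases count as events, and an inestimable term if they are excluded. CVD and the mortality outcomes are outside the problem.

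The practical harm ranges from a sentence that cannot be followed to serious inflation of discrimination. Which it is depends on how existing cases are handled, and the article does not state this. The AUC range of 0.63 to 0.95 applies only to the first case and rests on assumed frequencies; it is no forecast of the trial's results. The stated sample size of 4,199 is correct and not in dispute.

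**What to change.** For the type 2 diabetes, hypertension, obesity and hyper/dyslipidaemia models, state that:

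1. patients with that condition, by diagnosis or drug, at or before the index date are excluded from that model;
2. the condition's own diagnosis/medication term is removed from the retained set (in the diabetes model, the type 2 component);
3. all predictors are measured up to the index date only;
4. the same applies to the Table 2 lifetime comorbidity count and prescription items, if they are used as candidates.

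The cost is a few lines of analysis-plan text and some coding on register data. Where existing cases would otherwise have been counted, there will be fewer events and a lower reported C-index. The minimum sample size does not rise.

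Optionally, 5-year absolute risks for outcomes other than all-cause mortality could come from cause-specific Cox models for the event combined with models for death (for cause-specific mortality, death from other causes). This is a refinement, worth about 2.5–10% in relative terms at 5 years under assumed death rates of 1–4% per year, and not the correction of a demonstrated error.

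### The registry study's machine-learning plan chooses its final model on the test set, so the reported accuracy is a slightly optimistic best of four and no untouched data remain to correct it

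*Protocol article*

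**What the plan says.** The plan is in the Protocol article, Data analyses, Study 1: the registry study.

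- **Split:** "the data will be split into a 60% training set, 20% validation set, and 20% test set". The three parts add to 100%.
- **Candidates:** "Four models will be trained: penalized Cox regression, random survival forest, gradient boosting machine, and survival support vector machine".
- **Validation set:** "Hyperparameters will be tuned on the validation set". No other use is given.
- **Test set:** "Performance metrics on the test set will determine the final model".
- **Metrics:** "Model discrimination will be evaluated with C-index and cumulative/dynamic AUC", and then "Calibration will be assessed with the Integrated Brier Score".

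The standard Cox models in the same section are handled differently. For these, "A bootstrapping method will be used for internal validation of the models with 200 bootstrap samples", and "To assess the calibration of the models we will use the Integrated Brier Score and calibration plots".

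The section gives the purpose of the machine-learning work as exploring whether such algorithms, with many predictors, predict more accurately.

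**The concern.** A three-way split is useful because the third part is opened once, on a model that is already fixed. Here the third part decides which of four algorithms wins. It then works as a second validation set, and the winner's test figure is a selected maximum. Part of its lead is chance in that particular 20%.

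Nothing else in the article supplies an untouched estimate. The bootstrap is described for the Cox models. The separate assessment in Sweden and Norway divides the same register data. The check of the clinical support tool uses 5–10 clinical-study patients per country and baseline metabolic syndrome, so it cannot validate register risk models for cardiovascular disease or type 2 diabetes.

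The comparison of machine learning with conventional modelling is therefore at stake. If the Cox comparator is judged without such a selection, all of the optimism in the winner's figure passes into the apparent gain.

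A smaller issue concerns calibration. The Integrated Brier Score is an overall prediction error that mixes discrimination and calibration. For the Cox models plots stand beside it; for the machine-learning models it stands alone.

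**Working it through.** **No plan figure to reproduce on this point.** The article gives no optimism and no sample size for the machine-learning models. Its only computable Study 1 size is the Cox minimum, which reproduces: 24 / [(0.90 − 1) × ln(1 − 0.05/0.90)] = 4,198.9, that is 4,199. It does not bear on the selection problem.

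**Inputs from the article** (Power and sample size, Study 1): 40,000 patients and 12,000 events. Applying the split:

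- training 0.60 × 40,000 = 24,000
- validation 0.20 × 40,000 = 8,000
- test 0.20 × 40,000 = 8,000, with 0.20 × 12,000 = 2,400 events
- remainder 0

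**Assumptions, not in the article:** these counts apply to the machine-learning data; the C-index decides the choice; the four models have the same true C-index, taken as 0.75; their test errors have a common correlation ρ of 0.5 to 0.8.

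**Step 1, standard error.** The Hanley–McNeil formula (a binary-outcome approximation that ignores censoring), with n1 events and n0 non-events, is

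variance = [C(1 − C) + (n1 − 1)(a − C²) + (n0 − 1)(b − C²)] / (n1 × n0), where a = C/(2 − C) and b = 2C²/(1 + C).

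At C = 0.75, a = 0.600, b = 0.6429 and C² = 0.5625. With n1 = 2,400 and n0 = 5,600:

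variance = [0.1875 + 2,399 × 0.0375 + 5,599 × 0.0804] / 13,440,000 ≈ 540.1 / 13,440,000 ≈ 0.0000402, so SE ≈ 0.0063.

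**Step 2, best of four.** The expected maximum of four independent standard normals is 1.03 (simulated). With common correlation ρ, the optimism is 1.03 × √(1 − ρ) × SE:

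- ρ = 0.5: 1.03 × 0.707 = 0.73 SE
- ρ = 0.8: 1.03 × 0.447 = 0.46 SE

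**Step 3, result at C = 0.75.**

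| Test patients | Test events | SE | Optimism, ρ = 0.5 | Optimism, ρ = 0.8 |
|---|---|---|---|---|
| 8,000 | 2,400 (from stated totals) | 0.0063 | 0.0046 | 0.0029 |
| 8,000 | 400 (assumed) | 0.0143 | 0.0104 | 0.0066 |
| 8,000 | 160 (assumed) | 0.0225 | 0.0164 | 0.0104 |
| 800 (assumed) | 240 (assumed) | 0.0201 | 0.0146 | 0.0092 |

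For the first row, letting C run from 0.70 to 0.80 and ρ from 0 to 0.9 widens the range to about 0.002–0.007.

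**Step 4, after the fix.** If the algorithm is chosen without the test set, the selection optimism in the single test estimate is 0 in expectation.

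**Step 5, Brier score and calibration.** A simulated example used the ordinary Brier score for a binary outcome. A weak but calibrated model (calibration slope 0.98) scored 0.211. A stronger but over-confident model (slope 0.67) scored 0.171, where lower is better; the true probabilities scored 0.167. The score preferred the miscalibrated model because it discriminated better. A good score therefore does not show that predicted risks are right.

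**The case against.** **The bias is small where the article gives figures.** This stands. At 2,400 test events it is a few thousandths of the C-index. Four equally good models is also close to the worst case, and a clear winner would shrink the bias. The machine-learning work is exploratory and separate from the standard Cox models.

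**The test set may not be 8,000 patients.** This also stands. The Cox models are Swedish, the machine-learning models use Swedish and Norwegian registers, and the article does not say whether 40,000 covers one country or both. A larger test set means less bias.

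**The gap might not be in the full analysis plan.** This does not answer the main point. The article states a selection rule; it does not merely leave one out.

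A reader might infer more than the article supports:

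- *That the optimism is about as large as the gain being sought.* No target or expected gain in the C-index is stated. The figure of about 0.016 needs 160 test events, a number without a source in the article.
- *That a mis-selected machine-learning model will drive the clinical risk calculator.* The section on the clinical support tool does not say which model underlies it, and ease of use by clinicians is claimed for the Cox model.
- *That the Integrated Brier Score is no calibration measure at all.* It has a calibration component; it cannot isolate it.
- *That the plan is faulty because a survival support vector machine ranks patients and needs a further step to give risks.* An article may leave that step to the analysis plan.

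**Conclusion.** The concern holds in a limited form and should be fixed. As written, the final machine-learning model is selected on the test set, its reported performance is a best-of-four maximum, and no data are left for an unbiased estimate. The direction of the bias favours machine learning on the very question that the work is meant to answer.

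The size is about 0.003–0.005 in the C-index, given 8,000 test patients with 2,400 events, equally good models and error correlation 0.5–0.8. It would be larger for rarer outcomes or smaller genotyped subsets, but every figure for those rests on assumed counts. The standard Cox models' own validation is not affected.

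The calibration point is secondary. The sole measure named for the machine-learning models cannot by itself reveal over- or under-prediction, and the article already plans a suitable complement for the Cox models.

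**What to change.** Replace the selection sentence so that:

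1. both the hyperparameters and the algorithm are chosen on the validation set, or by cross-validation within the 80% outside the test set;
2. the choice is frozen before the test set is opened;
3. the chosen model is evaluated once on the test set, with confidence intervals, beside the standard Cox model fitted without the test patients;
4. test results for the other three algorithms are reported as descriptive only.

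Describe the Integrated Brier Score as overall accuracy, and extend to the machine-learning models the calibration plots already planned for the Cox models.

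The cost is a few sentences and a little more analysis work. No new data are needed. The reported performance may look slightly less favourable. The change has to come before the test set is used, because its independence cannot be recovered afterwards.
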